## Abstract

**Background:**

Occiput posterior position is the most common malpresentation in labour, contributes to about 18% of emergency caesarean sections and is associated with a high risk of assisted delivery. Caesarean section is now a major contributing factor to maternal mortality and morbidity following childbirth in developed countries. Obstetric intervention by forceps and ventouse delivery is associated with complications to the maternal genital tract and to the neonate, respectively.

There is level 2 evidence that prophylactic manual rotation reduces the caesarean section rate and assisted vaginal delivery. But there has been no adequately powered randomised controlled trial. This is a protocol for a double-blinded, multicentre, randomised controlled clinical trial to define whether this intervention decreases the operative delivery (caesarean section, forceps or vacuum delivery) rate.

**Methods/Design:**

Eligible participants will be (greater than or equal to) 37 weeks’ with a singleton pregnancy and a cephalic presentation in the occiput posterior position on transabdominal ultrasound early in the second stage of labour. Based on a background risk of operative delivery of 68%, then for a reduction to 50%, an alpha value of 0.05 and a beta value of 0.2, 254 participants will need to be enrolled.

This study has been approved by the Ethics Review Committee (RPAH Zone) of the Sydney Local Health District, Sydney, Australia, and protocol number X110410.

Participants with written consent will be randomised to either prophylactic manual rotation or a sham procedure. The primary outcome will be operative delivery (defined as vacuum, forceps and/or caesarean section deliveries). Secondary outcomes will be caesarean section, significant maternal mortality/morbidity and significant perinatal mortality/morbidity.

Analysis will be by intention-to-treat. Primary and secondary outcomes will be compared using a chi-squared test. A logistic regression for the primary outcome will be undertaken to account for potential confounders.

The results of the trial will be presented at one or more medical conferences. The trial will be submitted to peer review journals for consideration for publication. There will be potential to incorporate the results into professional guidelines for obstetricians and midwives.

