### Trial design

The POP-OUT trial is designed as a superiority, double-blinded, multicentre, randomised controlled clinical trial with two parallel groups and a primary endpoint of operative delivery. Randomization will be performed as block randomization with a 1:1 allocation.

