### Sample size

The sample size (254) was calculated on the basis of the primary outcome. The power calculation was based on our prospective cohort study of 160 women that was completed in May 2009 [3] and showed an operative delivery rate of 68% in the OP group, and from our survey of obstetricians conducted in 2010, who indicated they would perform a manual rotation for OP position if it reduced the rate of operative delivery from 68% to 50% [10]. To detect a reduction in the rate of operative delivery from 68% in the control group to 50% in the intervention group, a sample size of 127 women in each group (total = 254) will be required to have 80% power of finding a result. Alpha = 0.05 (2-tailed), Beta = 0.20 (Epi-Info version 3.3.2).

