### Analysis

Analysis will be by intention-to-treat (according to treatment allocation), including withdrawals and losses to follow-up. Losses to follow-up for the primary outcome are not expected because randomisation will occur at full dilatation and the primary outcome is the mode of delivery.

The results will be reported according to CONSORT guidelines.

Demographics and other potential confounders will be compared by treatment allocation in a univariate analysis. Categorical outcome measures will be compared by proportions (chi-squared test), means for normally distributed data (*t*-test), or rank order for non-normally distributed data (Mann–Whitney-*U* test).

A logistic regression analysis of treatment allocation and other variables on the primary outcome measure, operative delivery, will be performed. The following variables will be considered for the logistic regression model: maternal body mass index, maternal age, maternal height, maternal ethnicity, gestation, induction of labour, gestational diabetes, neonatal gender, and RCOG CTG classification in the second stage of labour. Parity, study site and the presence of epidural for intrapartum analgesia at the time of randomisation will not be included because randomisation is stratified for these variables. Only variables where *P* <0.25 in the univariate regression will be included in the multivariate model. Continuous variables that do not show a linear association with the logit function will be divided into quartiles and treated as categorical. Interaction terms will be considered for treatment allocation versus each of the other variables and where clinically appropriate between non-treatment variables. *P* <0.01 will be considered evidence of interaction. Terms will be excluded from the model in a stepwise backward manner until all remaining terms are both statistically significant (*P* <0.05) and clinically significant (that is, removal of the term results in a clinically significant change in the estimate of the odds ratio of treatment allocation for the primary outcome). The analysis will be performed using SAS 9.2 (or a more recent version of SAS).

Subgroup analyses will be performed according to the technique of manual rotation employed (manual/whole hand versus digital/fingers) and according to operator ability (data will be divided into two approximately equal groups according to the success rate of the operator who performed the manual rotation).

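### The Analysis section does not say whether the chi-squared test or the data-selected logistic model decides the trial, and it leaves parity, site and epidural out of the model for a reason that argues for including them

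*Protocol article*

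**What the plan says.** The Abstract (Methods/Design) states: "Primary and secondary outcomes will be compared using a chi-squared test". It then adds the logistic model: "A logistic regression for the primary outcome will be undertaken to account for potential confounders".

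The Analysis section keeps both. Categorical outcomes are compared by chi-squared test, and "A logistic regression analysis of treatment allocation and other variables on the primary outcome measure, operative delivery, will be performed". The covariates of that model are settled from the trial data:

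- Nine candidates are named and screened at P<0.25 in univariate regression.
- The survivors go through backward elimination at P<0.05.
- A term must also shift the treatment odds ratio by a clinically meaningful amount when removed. No threshold is given.

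On the stratification factors the section says: "Parity, study site and the presence of epidural for intrapartum analgesia at the time of randomisation will not be included". The reason given is that randomisation is already stratified by them. The Randomization/allocation concealment section explains why they were chosen as strata: each may be strongly related to operative delivery.

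The Sample size section plans for one comparison of two proportions, two-sided alpha 0.05: "a sample size of 127 women in each group (total = 254) will be required to have 80% power of finding a result". Neither the Abstract nor the Analysis section calls either analysis primary, supportive or a sensitivity analysis, or says which prevails if they differ.

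**The concern.** There are two linked problems.

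**No order.** One hypothesis has two planned analyses, and the covariates of one are known only after the outcomes have been seen. If one falls below 0.05 and the other does not, the article gives no rule for the conclusion. The Background expects a positive result to change practice, so the deciding analysis should be settled beforehand.

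**Strata left out for the wrong reason.** Stratified randomisation balances the arms on parity, site and epidural, so the between-stratum variation in outcome no longer contributes to the variance of the treatment difference. An unadjusted test still counts that variation in its standard error. The test is then too cautious and loses power. Neither planned analysis uses these three factors, although the protocol itself singles them out as likely strong predictors.

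**Working it through.** **1. Reproduce the sample size.** Inputs from the Sample size section: p1 = 0.68, p2 = 0.50, difference d = 0.18, two-sided alpha 0.05, power 80%. The mean proportion is (0.68 + 0.50)/2 = 0.59.

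- Uncorrected: n = [1.96·√(2·0.59·0.41) + 0.8416·√(0.68·0.32 + 0.50·0.50)]² / 0.18² = (1.3633 + 0.5755)² / 0.0324 = 116.0, so 117 per group (234 in total).
- Continuity-corrected: (116.0/4)·[1 + √(1 + 4/(116.0·0.18))]² = 126.9, so 127 per group (254 in total).

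The corrected formula reproduces the stated 254 exactly. At 127 per group the uncorrected test has power Φ[(0.18·√127 − 1.3633)/0.6838] = Φ(0.973) = 83.5%. The trial is therefore sized for an unadjusted comparison of two proportions, tested once.

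**2. Cost of ignoring the strata.** Let p_s be the event rate in stratum s. With n per arm, the unadjusted test uses the variance p̄(1−p̄)·2/n. Under stratified randomisation the variance is about [p̄(1−p̄) − Var(p_s)]·2/n. The unadjusted standard error is therefore too large whenever the strata predict outcome.

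Simulation: 254 women, blocks of 4 within parity × epidural, assumed 70% nulliparous and 70% with epidural, stratum log odds ratios from 0.7/0.7 to 1.5/1.2, site not modelled, chi-squared without continuity correction, 4,000 trials per setting.

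| | Chi-squared | Adjusted for parity and epidural |
|---|---|---|
| Rejection under no effect | 4.7% down to 3.3% | 4.9% to 5.3% |
| Power, 68% vs 50% | 84.1% to 85.4% | 85.3% to 89.2% |

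The gain in power runs from 85.3 − 84.1 = 1.2 points with weak strata to 89.2 − 85.4 = 3.8 points with strong strata. A second, separate simulation agreed: 83% to 85% against 85% to 89%, with null rejection of 4.7% to 3.4% against 5.2% to 4.9%.

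**3. Error rate if either test could be quoted.** Simulation under no effect: 254 women, about 68% events, nine candidate covariates, the stated P<0.25 screen and backward elimination at 0.05, treatment always kept in the model, 3,000 trials per run. Ranges cover repeated runs or settings.

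| Assumed covariates | At least one test below 0.05 |
|---|---|
| None prognostic | 5.6% |
| Three moderate (log odds 0.4 per SD) | 6.5% to 6.7% |
| Five strong (log odds 0.6 per SD) | 7.2% to 8.4% |
| Moderate or strong, with strata also prognostic | 5.8% to 6.4% |

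Each test alone stayed near 5%: chi-squared 4.2% to 5.5%, logistic 4.2% to 5.8%. The Monte Carlo standard error is about 0.4 to 0.5 points.

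**4. How often the two would disagree.** With a true treatment log odds ratio of −0.5, the tests differed on significance in 10.8% of trials (moderate covariates) and 16.2% (strong covariates plus strata). For scale, the planned effect is ln(0.50/0.50) − ln(0.68/0.32) = −0.75, so −0.5 is about two thirds of it.

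The documents give no covariate or stratum strengths, so all of those are assumptions. The simulations do not model the rule on shifts in the treatment odds ratio, which has no threshold, or interaction terms in the final model.

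**The case against.** The strongest reply is that the chi-squared test is primary in all but name. It is listed first, the logistic model is given the separate purpose of accounting for confounders, and the sample size matches an unadjusted comparison exactly. On that reading the 5% level is kept. The P<0.05 in the model-building rules is a criterion for retaining terms, not a declared second test of efficacy. This stands.

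A reader might infer that the trial's 5% error rate is already broken. The documents do not support that, because they nowhere allow success to be claimed on either test. A reader might also infer that covariates can be chosen freely to reach significance. The Analysis section does not allow that either: it names nine candidates and a set screening and elimination procedure.

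It can also be said that ranking the analyses is commonly left to a full protocol or an analysis plan, neither of which is shown. As to the missing order alone, that is fair. It does not cover what the Analysis section itself fixes: a model selected on the outcome data, a retention rule that depends on the treatment estimate and has no threshold, and an explicit exclusion of the stratification factors on reasoning that points the other way.

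Finally, leaving out the strata does not inflate the false-positive rate. That is correct. It makes the unadjusted test cautious, and the cost is power.

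**Conclusion.** The point holds in a limited form. The article plans two analyses of one primary outcome without ranking them, and the Analysis section wrongly treats stratification as a reason to leave parity, site and epidural out.

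- **Power:** about 1 to 4 points lost at 68% vs 50%, given assumed parity and epidural effects and no site effect.
- **False positives:** kept at 5% if the chi-squared test is primary. Not guaranteed if either test may be quoted, with a rate of about 5.6% to 8.4% under assumed covariate strengths. Because the two tests are highly correlated, the excess is modest.
- **Conflicting conclusions:** about 11% to 16% of trials at a moderate true effect, with no rule in the article to settle them.

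This does not invalidate the trial or its sample size. It is worth correcting because the correction costs almost nothing and removes an avoidable dispute about the result.

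**What to change.** In the Analysis section:

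1. Delete the sentence that excludes parity, site and epidural from the model.
2. Name one primary analysis, fixed in advance, at two-sided 0.05: operative delivery on allocation, adjusted for parity, epidural and site. The text at hand does not give the number of sites, so state beforehand that small sites will be pooled, or that a stratified Mantel-Haenszel test will be used if site cells are sparse.
3. Label the unadjusted chi-squared test and the model with selected covariates as supportive, with no claim of efficacy resting on either alone.

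Naming the chi-squared test as primary would also settle the order and keep the 5% level, but it would forgo the power gained by adjustment.

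The cost is a few sentences in the protocol or analysis plan, through the amendment route that the protocol describes. N stays 254 and no new data are needed, because the three factors are recorded for randomisation. The Trial status section reports 160 recruited, so on that status the change can be made before recruitment is complete.

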**Trial registration:**

The Australian New Zealand Clinical Trials Registry ACTRN12612001312831. Trial registered 12 December 2012.

## Background

Persistent occiput posterior (OP) position is associated with 18% of intrapartum caesarean sections and a high risk of assisted vaginal delivery [1-3]. Caesarean section is now a major contributing factor to maternal mortality and morbidity following childbirth in developed countries [4,5]. Obstetric intervention by forceps and ventouse delivery is associated with complications to the maternal genital tract and neonate, respectively [6-8].

Manual rotation from the OP to the occiput anterior (OA) position is a safe, relatively simple and easy to perform procedure that could reduce the operative delivery rate (defined as vacuum delivery, forceps delivery and/or caesarean section) and therefore increase the chances of a normal vaginal birth [9]. It is performed by only a minority of obstetricians and midwives in Australia and New Zealand, yet is considered to be acceptable by the vast majority [10,11]. However, obstetricians and midwives would perform a manual rotation if there was evidence that it reduced the risk of operative delivery to 50% or less [10,11] suggesting that demonstration of efficacy will translate into clinical practice.

Preliminary studies of efficacy are promising, but there has been no adequately powered randomized controlled trial (RCT) [12,13]. It has been recommended that RCTs be conducted to explore the efficacy of manual rotation in the management of OP labours [14].

### Epidemiology

The prevalence of the OP position is 15 to 32% at the onset of labour [15-18], 10 to 20% early in the second stage of labour and 5 to 8% at delivery [2,17,19,20]. The operative delivery rate varies from 54% to 82% when the OP position is present at delivery, compared with 6% to 22% when the fetus is in the more common OA position [3,16,19,20]. When the OP position is present at the beginning of the second stage of labour, the operative delivery rate was about 70% in two higher risk cohorts [2,3].

Thus, of all women who plan to have a normal vaginal birth, 10 to 20% will have a fetus in the OP position early in the second stage of labour. These women will be eligible to have a manual rotation to modify their background risk of up to 70% of obstetric intervention with forceps, vacuum or caesarean section.

### Complications of the occiput posterior position

The OP position is associated with more frequent induction and augmentation of labour and prolonged first and second stage of [3,17,18,21], chorioamnionitis, post-partum haemorrhage, third and fourth degree perineal tears, wound infection and endometritis [22,23]. Associated adverse neonatal outcomes include birth trauma, low 5-minute Apgar score, and admission to the neonatal intensive care unit [24].

### The intervention in current practice

Manual rotation is a well-accepted component of obstetric practice, particularly in the context of rotating the fetus to the OA position immediately prior to the application of non-rotational forceps such as Neville-Barnes [25]. However, it is also used commonly in a prophylactic setting (without assisted delivery) to reduce the complications associated with OP delivery [12,13]. In a survey of obstetricians in Australia and New Zealand, 70% believed it was acceptable in a prophylactic setting; but only 38% had performed a manual rotation in the last year, and most of these had only performed one or two [10]. Both obstetricians and midwives reported they would perform a manual rotation if there was evidence that it would reduce the chances of operative delivery from 68% to 50% or less [10,11]. Thus demonstration of efficacy would provide substantial scope for the intervention to be introduced into widespread practice.

### The efficacy of the intervention

Preliminary cohort studies report that manual rotation is associated with a reduction in caesarean section and adverse maternal outcomes:In a retrospective cohort study, Schaffer *et al.* (2006) (n = 731) reported that the caesarean section rate was lower in women who had a successful manual rotation compared to when the fetus was unable to be rotated (2% versus 34%) [26]. However, there was no control group of women for whom a manual rotation was not performed and it is not possible to know if this was due to the procedure itself or to underlying confounders such as a smaller fetus.In a prospective cohort study with historical controls (n = 61), the local labour ward policy was changed from not performing prophylactic manual rotation to routinely performing the procedure for OP position about ‘half way’ into the second stage of labour [12]. The operative delivery rate for fetuses in the OP position fell from 73% prior to the change in policy to 23% after the policy was implemented, but this study design is subject to a significant risk of bias.Schaffer *et al*. (2011) re-reported their 2006 data with a control group identified retrospectively from a database and found a 9% risk of caesarean section when manual rotation was performed compared with a 41% risk when it was not [13]. However, the authors had information on the fetal position at the time of birth but not earlier in the second stage of labour when the procedure was performed. Thus OP fetuses that were destined to rotate naturally to the OA position would have been included in the intervention group, but not the control group, which would result in an overestimation of the caesarean section rate in the control group and of the efficacy of manual rotation.

Thus preliminary studies suggest that manual rotation reduces the risk of operative delivery but are susceptible to significant bias. An RCT would best provide unbiased answers regarding the effects of manual rotation of the fetal occiput on maternal and perinatal outcomes.

### The safety of the intervention

Manual rotation has long been considered to be safe [9]. One retrospective cohort study reported lower rates of complications when it was performed for OP position compared to when it was not (Table 1) [13]:

**Table 1 Tab1:** **Complications of manual rotation versus expectant management (Shaffer 2011)** [13
**]**

**Complication**	**Manual rotation (n = 731)**	**Expectant (n = 2,527)**	***P***
Postpartum haemorrhage	22.3%	33.1%	<0.001
3^rd^ and 4^th^ degree tears	15.7%	20.1%	0.017
Cervical laceration	2.2%	1.0%	0.024
Chorioamnionitis	8.6%	14.4%	<0.001
Endometritis	3.6%	7.2%	<0.001
5-min Apgars <7	1.8%	3.7%	0.011
Umbilical cord arterial pH			
<7	0.6%	1.4%	0.15
Base excess < −12	3.5%	3.2%	0.73
Shoulder dystocia	2.1%	1.1%	0.064
Birth trauma	1.09%	1.23%	0.77

Thus, third and fourth degree tears, chorioamnionitis, post-partum haemorrhage, endometritis and 5-minute Apgars less than 7 all improved when prophylactic manual rotation was performed. but cervical laceration was increased.

In the POP-OUT trial manual rotation will be performed at full dilatation, which theoretically will minimize the risk of cervical laceration.

There is also a single case report of an umbilical cord prolapse associated with a manual rotation [27]. In this report, an emergency caesarean section was performed and the baby was born alive and presumably well. Other risk factors such as amniotomy, application of a fetal scalp electrode and external cephalic version were more frequently associated with umbilical cord prolapse [27].

### The timing of the intervention

Manual rotation from the OP position may be performed at full cervical dilatation or late in the first stage of labour. In a French case control study (n = 147) in a labour ward where prophylactic manual rotation was performed routinely, two risk factors for inability to rotate the fetus were identified: [1] attempted rotation before full dilatation and [2] failure to progress in labour [28]. Thus. we consider that it would be reasonable to attempt prophylactic manual rotation after full dilatation is achieved, but relatively early in the second stage of labour, before the fetal head becomes impacted in the maternal pelvis.

### Rationale for operative delivery as the primary outcome

Operative delivery was selected as the primary outcome for the POP-OUT Trial because it is clearly associated with important short- and long-term outcomes for the woman and her baby [6-8,29-32]. Other important obstetric parameters will be measured, but reported as secondary outcomes. Reducing the rate of operative delivery for OP position is perceived to be very important by obstetricians and midwives [10,11]. In high income countries, emergency caesarean section is associated with significant maternal morbidity and a fivefold increase in maternal mortality [33].

### Explanation for choice of comparator

A sham procedure was chosen as a comparator to minimize the risk of performance bias. There would be substantial scope for management to differ according to treatment allocation if it was known. For example, a women could be encouraged to push more strongly if her midwife was aware that a manual rotation had been performed.

